### Provisions for post-trial care {30}

At the end of 12 months of post-randomisation follow-up, participants will be given the option to be told which group they were randomised to. If they were allocated to the diagnostic laparoscopy alone group, they will have the opportunity to discuss whether they wish to have surgical removal of SPE as a component of their routine NHS gynaecological follow-up.

### Outcomes {12}

The primary outcome in this trial is the ‘pain domain’ of the Endometriosis Health Profile-30 (EHP-30) questionnaire at 12 months post-randomisation.

EHP-30 is a commonly used, condition-specific, patient reported outcome questionnaire that assesses health-related quality of life in endometriosis across five key domains (pain, control and powerlessness, emotional well-being, social support, and self-image) [14]. Evaluation of EHP-30 has shown consistent acceptability, validity, reliability and sensitivity to change suitable for use within endometriosis research and clinical trials of endometriosis interventions [15, 16].

Secondary clinical outcomes will include measures of use of hormones and analgesics, occupational impact, post-operative pain and reproductive outcomes. Secondary outcomes are detailed as follows:Time off work and presenteeism defined by the Work Productivity and Activity Impairment Questionnaire (WPAIQ) at 12 monthsNeed for hormonal medication for endometriosis-related symptoms at 3, 6 and 12 monthsNeed for analgesics for endometriosis-related symptoms at 3, 6 and 12 monthsPain domain of the EHP-30 at 3 and 6 monthsTotal score of EHP-30 at 3, 6 and 12 monthsFatigue symptoms defined by the Brief Pain Inventory (BFI) at 12 monthsNeuropathic pain features identified by PainDETECT™ at 12 monthsUrinary symptoms defined by Pelvic Pain and Urinary Frequency (PUF) Patient Symptom Scale at 12 monthsIrritable bowel symptoms defined by the ROME IV Criteria at 12 monthsPain catastrophizing measured by Pain Catastrophizing Questionnaire (PCQ) at 12 monthsFibromyalgia defined by Fibromyalgia Scale (FS) at 12 monthsSpecific patient reported symptoms defined by Measure Yourself Medical Outcome Profile 2 (MYMOP2)Post-operative (up to 7 days after surgery) pain and analgesic requirements by patient reported diaryLength of hospital stayAdverse events related to surgery at 30 daysSurgical complications at 30 daysSurgical operating timeNeed for further surgery for endometriosis related symptoms at 12 monthsPregnancy events at 3, 6 and 12 months

Outcomes used for the economic evaluation will include:Utility values, derived from EQ-5D-5L health-related quality of life score at 3, 6, and 12 monthsGeneral wellbeing defined by Capability Questionnaire (ICECAP-A) at 3, 6, and 12 monthsCosts and resource use at 3, 6 and 12 months (primary and secondary care use)Impacts on employment, caregiving, and other usual activities (e.g. education)

For those allocated to surgical removal, we will also report the operative technique for removal of endometriosis (excision, ablation, or combination) and adequacy of removal of endometriosis (subjective and independent). Subject to further funding we aim to compare future fertility and need for further surgery using data linkage and assess EHP-30, ROME IV, PUF, EQ-5D-5L, PainDETECT™, hormonal and analgesic use, fertility interventions and pregnancy events measured at 2 and 5 years post-randomisation.

### Participant timeline {13}

A schedule of events for participants is detailed in Table 2.

**Table 2 Tab2:** Trial composite questionnaires can be completed in person, via telephone, via post or via online link (*). Follow-up outcome questions are completed via a telephone call (**). Consent confirmed if initial consent was via telephone (***). NB: Longer term follow-up not shown in this table as not funded at time of writing

Phase	Baseline	Randomisation (day of surgery)	Days 1–7 post-operatively (± 1 week)	30 days post-operatively (± 1 week)	3 months post-operatively (± 2 weeks)	6 months post-operatively (± 2 weeks)	12 months post-operatively (± 2 weeks)
Consent to trial	**x**	**x*****					
Eligibility	**x**	**x**					
Medical history	**x**						
Post-operative pain diary			**x**				
Post-operative phone call (complications)				**x**			
Trial composite questionnaires*	**x**				**x**	**x**	**x**
Follow-up outcome form**					**x**	**x**	**x**
Adverse events				**x**			

### Sample size {14}

An 8-point difference of the EHP-30 pain domain is equivalent to a standardized difference of 0.36 (assuming a standard deviation of 22) and reduction in pain of this magnitude is considered clinically significant. Data from a UK endometriosis trial (PRE-EMPT ISRCTN97865475) shows a standard deviation (SD) of 19 (95% CI 16–22) in baseline EHP-30 scores [17]. Assuming an 8-point difference and a SD of 22, 160 participants are required in each treatment arm to detect that difference with 90% power and a two-sided 5% significance level. Assuming a maximum of 20% loss of primary outcome data, 400 randomised participants will be required. We acknowledge that the variability in our outcome may be different to that observed in the PRE-EMPT trial due to differences in the intervention; therefore, the ESPriT2 trial steering committee (TSC) will review blinded pooled EHP-30 data and advise whether the sample size should be reconsidered, if necessary.

### Recruitment {15}

We will randomise 400 participants (200 per trial group). To achieve this, we estimate we will need to consent 1000–1200 participants (based on our experience of recruiting to similar surgical endometriosis trials). Identification of potentially eligible ESPriT2 participants will occur via three pathways. Potentially eligible participants can be identified via gynaecology out-patient departments following a clinical decision to perform a diagnostic laparoscopy for the investigation of chronic pelvic pain. Alternatively, potentially eligible participants can be identified from diagnostic laparoscopy waiting lists and invited to participate, or individuals can self-refer after seeing trial promotional material.

## Assignment of interventions: allocation

### Sequence generation {16a}

Eligibility will be confirmed at the time of laparoscopy following a finding of SPE only. Participants will be randomised in 1:1 ratio to either diagnostic laparoscopy alone or to concurrent surgical removal (ablation/excision/combination of both) using a remote randomisation system provided independently by Edinburgh Clinical Trials Unit (ECTU). Randomisation will use a computer-based randomisation system stratified using permuted blocks by the following important prognostic variables:Presence of dysmenorrhoea (yes/no)Pre-operative hormone treatment (yes/no)Presence of dyspareunia (yes/no)

### Concealment mechanism {16b}

The participant’s intraoperative data will be entered into a 24-h computerised central randomisation service by means of a secure web interface or by a telephone call to the trial management team.

### Implementation {16c}

The ECTU randomisation service determines the treatment allocation and will be given to the operating surgeon. If the database is not available, emergency randomisations will be performed by simple randomisation using a computer-generated random number list provided independently by ECTU. The allocation sequence will be enclosed in sequentially numbered, opaque, sealed envelopes. Envelopes are opened by the research team only after the enrolled participant has eligibility confirmed, and the treatment allocation will be given to the operating surgeon.

## Assignment of interventions: blinding

### Who will be blinded {17a}

This is a participant blind trial. Participants will be informed of a diagnosis post-operatively but will not be informed if surgical removal was carried out. All attempts will be made to minimise the inadvertent unblinding of all trial participants. This will include providing templates for operative findings and standardised discharge letters. The operation note will include only the operative findings but not treatment allocation or details of surgical removal (if applicable). These will be recorded within the surgical case report form (SCRF) and will be added to the individuals NHS records at the end of participation. Participants’ general practitioners will not be informed of whether surgical removal of SPE occurred during the trial period but will be informed when a diagnosis of SPE is made. Where feasible, the onward clinical management within secondary care will not be those who performed surgery. The importance of maintaining blinding will be emphasised to all members of the surgical care team, e.g. anaesthetic staff, theatre, and recovery staff, etc.

### Procedure for unblinding if needed {17b}

At the end of 12 months of post-randomisation follow-up, participants will be given the option to be unblinded. An unblinding facility will be available on the database. If it becomes necessary to unblind a participant prior (e.g. at the participant’s request or for emergency purposes), they will need to contact the local principal investigator (PI) and local research team who will follow the unblinding procedure on the trial database. This will be documented on the database with the reason why the unblinding has taken place as well as the date of the unblinding. Participants unblinded prior to 12 months will still be requested to complete trial outcome measures.

## Data collection and management

### Plans for assessment and collection of outcomes {18a}

#### Trial composite questionnaire

The trial composite questionnaire contains a range of validated patient-reported outcome measures. Responses to this questionnaire will be collected pre-operatively and then at 3, 6 and 12 months post-operatively (see Table 2). It can be completed in person, via telephone, via post or via online link. The baseline and follow-up trial composite questionnaire will include:Endometriosis Health Profile-30 (EHP-30) [14]o30 question and five scale endometriosis questionnaire (explained above)Rome IV Criteria [18]oThree questions to identify irritable bowel syndromePelvic Pain and Urinary Frequency (PUF) Patient Symptom Scale [19]oEight-point scale about urinary patterns and painPainDETECT.™ [20]o14-item questionnaire to identify neuropathic painBrief Fatigue Inventory (BFI) [21]oSix-item questionnaire correlated with standard quality of life measures assessing severity of fatigue and impact of fatigue on functioning over the previous 24 hPain Catastrophizing Questionnaire (PCQ) [22]o13-item scale, with each item rated on a 5-point scale. The PCQ is broken into three subscales being magnification, rumination, and helplessness. The scale was developed as a self-report measurement tool that provided a valid index of catastrophisingFibromyalgia Scale [23]oSeven questions related to fibromyalgia symptomsMeasure Yourself Medical Outcome Profile 2 (MYMOP2) [24]oPatient-generated outcome questionnaireWork Productivity and Activity Impairment Questionnaire (WPAIQ) [25]oQuestions related to the effect your health issues have on work and regular activitiesEuroQol 5 Dimensions 5 Level Questionnaire (EQ-5D-5L) [26]oTwo-part questionnaire with the EQ-5D descriptive system and the EQ visual analogue scale to assess patients’ health state in five dimensions: mobility, self-care, usual activities, pain/discomfort and anxiety/depressionCapability Questionnaire (ICECAP-A) [27]oCapability instrument for adults

The baseline and follow-up questionnaire differ where:The baseline questionnaire contains text prior to the EHP-30 as follows “This questionnaire asks about ‘symptoms due to endometriosis.’ We realise that you do not know whether or not you have endometriosis so please try and ignore the references to endometriosis and simply answer the questions focusing on the symptoms.”The questions in the MYMOP2 questionnaire are adapted in the follow-up questionnaires to account for the fact that the participant needs to remember how they answered this questionnaire at baseline.

### Trial follow-up outcome form

The trial follow-up outcome form documenting analgesic use, hormonal medication, pregnancy events and use of healthcare services will be collected at 3, 6 and 12 months post-operatively via telephone by the research team. Participants will also be asked about any impacts associated with their condition on their work, caring responsibilities or other usual activities (e.g. education).

### Surgical case report form

Following laparoscopy, the surgeon will complete a surgical case report form (SCRF) detailing information about the operation. For all participants this will be:Grade of surgeon and whether they self-identify as an advanced laparoscopic surgeonDiagnosis of endometriosis subtype (SPE, ovarian endometrioma, deep)Ovarian cyst present that requires removalConfirmation of eligibility to be randomisedDetails of SPE (location, number and appearance of lesions)Details of other findings (fibroids, adhesions, peritoneal pockets)Hysteroscopy/cystoscopy taking place during laparoscopy (yes/no)Pathology results if endometriosis is removed or deep disease or endometrioma found

For all randomised participants:Details of any tubal dye tests performedDuration of surgeryConcurrent intrauterine system/device insertionNumber and location of accessory ports, not including optical port.Intraoperative complications (e.g. uterine perforation, anaesthetic complication, injury to surrounding anatomy, haemorrhage, and laparotomy)Details of images captured for diagnosis

For randomised participants allocated to surgical removal of SPE:Type of removal will be recorded (excision, ablation or combined)Details of images captured showing any removalSubjective assessment of whether or not complete removal was achieved (and reasons for this)Histological result if SPE excised and sent for histological assessment

The SCRF includes a specific set of pre-determined images. For the diagnostic laparoscopy, this is a standard panel of images of the pelvis which include the uterovesical fold, pouch of Douglas and right and left ovarian fossa. If allocated to surgical removal, the type of surgical removal will be documented, and an assessment of the adequacy of removal and images of treated areas will be performed. Three independent clinicians will assess these images, blind to operating surgeon’s classification, to reduce the likelihood of misclassification and complete an electronic surgical verification form detailing extent of endometriosis and adequacy of removal (if carried out).

### Post-operative diary

Participants will be asked to complete a diary of analgesic use and numerical rating score for worst and average pelvic pain on days 1 to 7 post-operatively.

### Post-operative form

A post-operative form (part of the electronic data collection form (DCF) will be completed detailing complications up to 30 days post-operatively. This will be completed by the clinical research team, utilising information gained by a phone-call to the patient and correlated with the participant’s hospital record. Specific complications include urinary retention, unintended overnight stay, haemorrhage, transfusion, pelvic haematoma, visceral injury (bowel, bladder, ureteric), infection (urinary, chest, wound, pelvic abscess, other), venous thromboembolism, fistula, hernia, return to theatre, readmission, ITU admission and death. Any reportable adverse events (AE) will be collected up to 30 days post-operatively.

### Data collection form

At baseline, the following personal data will be collected from trial participants in the data collection form (paper or electronic via a secure web interface to the trial database): name, NHS number or community health index number (Scotland only), unique hospital number, email address, telephone number, home address, ethnicity and year of birth. On the day of randomisation, an electronic DCF will be completed by a member of trial team and will include current analgesic use, current hormone use, visits to primary and secondary care providers, postcode to determine deprivation index, clinical pregnancy test result, future fertility intent, occupation and education, presence of dysmenorrhea (yes/no), presence of dyspareunia (yes/no) and presence of cyclical pain without menses (yes/no).

### Plans to promote participant retention and complete follow-up {18b}

Participant retention strategies include flexibility in data collection method and timing. Participants can provide data in person or using telephone, online or postal methods with a 2–4-week window provided around each point of follow-up. Support is available from a clinical research nurse via telephone if a participant may experience distress when completing the trial questionnaires.

### Data management {19}

Electronic data will be stored on University of Edinburgh secure server which is password protected and access is limited according to trial role. The participant’s email address will be kept securely on the trial database for the purposes of follow-up. Data from the trial composite questionnaire, trial follow-up outcome form (DCF), post-operative form, and SCRF will be uploaded and stored on a secure database. Personal data will be stored for a minimum of 5 years by the research team in a locked cabinet with limited access in research offices in all centres. Surgical digital images will be anonymised and uploaded. If print out images are only available, these will be scanned and then uploaded via the secure web interface.

The University of Edinburgh and NHS Lothian are joint data controllers. Any data breaches will be reported to the University of Edinburgh and NHS Lothian Data Protection Officers who will onward report to the relevant authority according to the appropriate timelines if required.

### Confidentiality {27}

All evaluation forms, reports and other records will be identified in a manner designed to maintain participant confidentiality. All records will be kept in a secure storage area with limited access. Clinical information will not be released without the written consent of the participant. The investigator and trial site staff involved with this trial may not disclose or use for any purpose other than performance of the trial, any data, record or other unpublished information, which is confidential or identifiable, and has been disclosed to those individuals for the purpose of the trial. Prior written agreement from the sponsor or its designee must be obtained for the disclosure of any said confidential information to other parties.

### Plans for collection, laboratory evaluation and storage of biological specimens for genetic or molecular analysis in this trial/future use {33}

Participants consented to ESPriT2 will be offered the option of providing a venous blood sample (approximately 55 ml) for a separate biomarker study (ESPriT +). Standard processes regarding collection and processing of the samples will used by each participating site. Blood samples (serum and plasma) will be frozen and stored locally and then sent via a specialised courier to the trial management team within the University of Edinburgh. Part of the blood samples will be sent with consent to Roche Diagnostics, Penzberg, Germany, and part of the blood samples will be retained by the University of Edinburgh for future ethically approved studies. All samples will be coded and will only be identifiable via a unique participant number.

## Statistical methods

### Statistical methods for primary and secondary outcomes {20a}

Analyses will primarily be intention-to-treat where all randomised participants will be included in the analysis retained in the group to which they were allocated and for whom outcome data are available. All results will be presented as point estimates, 95% confidence intervals with associated *p*-values. We will specify all analyses to be undertaken in a statistical analysis plan to be finalised before database lock.

### Primary outcome analysis

The primary outcome, pain domain of the EHP-30 at 12 months, will be compared using a linear regression model to estimate the mean difference in outcome, including fixed effect terms for surgical removal group, baseline pain score and stratification variables. Unadjusted results will also be presented to support the findings of the primary analysis. Secondary analyses will include using repeated-measures (multi-level) models incorporating outcome data from other follow-up time points.

### Secondary outcome analysis

A similar approach to the primary analysis will be used for analyses of the other secondary outcomes, using an appropriate (depending on outcome type) regression model.

### Economic analysis

An economic evaluation will be conducted using trial data based on the primary economic outcome of cost per quality-adjusted life year (QALY) gained, with a secondary analysis of cost per clinically significant change in symptom score at 12 months (using EHP-30). The primary perspective adopted will be an NHS and personal social services perspective, but a wider societal perspective will also be pursued using trial data about impact on work productivity. The NHS resource use collected will include secondary care costs related to surgery, length of stay and complications/readmissions as well as primary care and other healthcare costs. If the trial demonstrates that laparoscopic removal is effective in the management of SPE, longer term costs and outcomes will be assessed as part of a decision-analytic model.

The primary analysis will be in the form of a cost-utility analysis using the EQ-5D-5L instrument (collected at baseline, 3 months, 6 months and 12 months) plus data on costs and resource use collected in the trial. For the cost-utility analysis, we will evaluate the cost per QALY gained at 12 months. A secondary analysis will use the EHP-30 (using the same approach as adopted for the clinical analysis) and evaluate the cost per clinically significant change in symptom scores at 12 months. For those allocated to surgical removal, the primary outcome data will be summarised by the surgical approach (excision, ablation, or combined). A range of sensitivity analyses will be conducted to explore the impact of uncertainty on the results.

### Interim analyses {21b}

For the internal pilot, we will use stop–go criteria based on a Green-Amber-Red statistical approach including sites recruiting over the first 18 months. Assuming each centre month follows an independent identically distributed Poisson distribution with mean 0.33 and an expected randomisation of 54 participants by the end of month 18, we will use the following stop–go criteria.‘Green’ will be within 1 standard deviations of 54, i.e. if we have randomised 46 or more with an average rate per centre per month of 0.28 we will continue unchanged.‘Amber’ will be within 1–4 standard deviations, i.e. if we randomise between 24 and 46 with an average rate per centre per month of 0.12, then we will modify (export identified best practice from best recruiting sites; and/or more sites; and/or more recruitment time).‘Red’ will be if we randomise less than 24 then consideration will be given to stopping the trial, including discussions with the funder (NIHR/HTA).

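### Internal-pilot stop–go criteria: the amber rate of 0.12 per centre-month does not match its own count of 24, which gives 0.15, and a count of 46 falls in both green and amber

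*Protocol article*

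**What the plan says.** The Protocol article, Interim analyses {21b}, bases the internal-pilot criteria on a "Poisson distribution with mean 0.33 and an expected randomisation of 54 participants by the end of month 18". Three bands follow.

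- **Green** "will be within 1 standard deviations of 54", put into figures as "if we have randomised 46 or more with an average rate per centre per month of 0.28". The trial then continues unchanged.
- **Amber** "will be within 1–4 standard deviations", put into figures as "if we randomise between 24 and 46 with an average rate per centre per month of 0.12". Recruitment arrangements are then modified.
- **Red** is fewer than 24 randomised, with no rate attached. Stopping is then considered, with the funder involved.

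Green and amber thus each carry three descriptions of the same limit: a distance in standard deviations, a count and a rate. The number of centre-months is not printed, but it follows from the mean and the expected total.

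**The concern.** The three descriptions of a limit should agree, because all of them derive from one Poisson mean and one expected total. At the lower limit of amber the rate looks too low for the count. The two printed pairs also seem to need different denominators: 46 at 0.28 and 24 at 0.12 cannot both come from one pilot with a fixed number of centre-months. In addition, the count of 46 closes the amber band and opens the green one.

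These limits are the article's numerical rule for whether the trial continues unchanged, is modified or is considered for stopping. Someone who checks recruitment against the printed amber rate would be using a limit about 18% too low (0.12 against 0.147). Someone with exactly 46 randomised would find two instructions.

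**Working it through.** **Inputs, all from Interim analyses {21b}:** Poisson mean 0.33 per centre-month; 54 expected by month 18; limits at 1 and 4 standard deviations (SD); printed pairs 46 with 0.28 and 24 with 0.12.

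**Derived base**
- Centre-months = 54 / 0.33 = 163.6
- SD of a Poisson total with mean 54 = √54 = 7.35

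**Figures that reproduce**
- Green count: 54 − 7.35 = 46.65, printed as 46 (rounded down; 46 is 8/7.35 = 1.09 SD below 54)
- Amber floor count: 54 − 4 × 7.35 = 24.6, printed as 24 (rounded down; 24 is 30/7.35 = 4.08 SD below 54)
- Green rate: 46 / 163.6 = 0.281, printed as 0.28

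**The figure that does not**
- Amber floor rate: 24 / 163.6 = 0.147, which is 0.15 to two decimals; printed as 0.12
- In reverse: 0.12 × 163.6 = 19.6 randomised, and (54 − 19.6) / 7.35 = 4.7 SD below 54, outside the 4-SD limit
- Implied denominators: 46 / 0.28 = 164 centre-months, but 24 / 0.12 = 200

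**Could rounding or another derivation explain 0.12?**
- Mean of exactly 1/3: 162 centre-months, 24 / 162 = 0.148
- Mean anywhere from 0.325 to 0.335: 166.2 to 161.2 centre-months, rate 0.144 to 0.149
- Rate from the unrounded 4-SD limit: 24.6 / 163.6 = 0.150
- Limit worked on the rate scale: 0.33 − 4 × √(0.33/163.6) = 0.150
- Rate of 0.12 itself rounded (0.115 to 0.125): 24 / 0.125 = 192 to 24 / 0.115 = 209 centre-months, still far from 164
- Midpoint of the amber band, in case 0.12 was meant as a typical rate: 35 / 163.6 = 0.21

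None gives 0.12.

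**The shared limit.** Green starts at 46. Red covers everything under 24, so 24 itself must be amber and the amber range has to be read as including its end points. Read that way it also includes 46, which is already green.

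**The case against.** The strongest reply is that the error changes no decision. Red is defined by count alone, and amber requires at least 24 randomised as well as the attached rate. A reader might infer that 20 to 23 randomised is red by count but amber by rate. The text does not support that: 20 to 23 fails amber's own count condition and is red as written, and no rule is stated under which the stopping discussion begins at a rate of 0.12. At the planned number of centre-months the wrong rate reclassifies nothing. This part of the reply stands.

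A second reply is that the timing makes the point largely historical. The Trial status section reports a start on 1 April 2021 and 89 randomised at submission, well above 46. That makes it likely that the pilot passed, but the article gives neither the count at month 18 nor the submission date, so it is not established.

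A third reply is that the overlap concerns one integer and is loose wording, since green names 46 explicitly. That is fair, and it is why the overlap is only a wording correction.

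None of these replies makes 0.12 agree with 24. Both figures are current printed text in one sentence, so the contradiction does not depend on what a fuller protocol or analysis plan might add.

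**Conclusion.** The point holds in a narrow form. One printed figure is wrong: the amber rate of 0.12 should be 0.15 to match the count of 24 and the 4-SD limit. The discrepancy is 0.027 per centre-month, or about 4.4 participants (24 against 19.6). One wording fault goes with it: 46 belongs to two bands.

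A reader might go further and infer that the thresholds as a whole do not follow from their stated basis, or that they should move to 47 and 25 because 46 and 24 lie slightly beyond 1 and 4 SD. The documents do not support either. Both counts are the computed limits rounded down, the green rate agrees with its count, and moving the limits would rewrite pre-specified criteria over rounding.

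The result rests on the printed mean of 0.33 and total of 54, from which the centre-months are derived. Across the rounding range of 0.33 the rate for 24 stays between 0.144 and 0.149. The practical effect is modest: classification by count is intact apart from the single value 46, and the sample size and primary analysis do not depend on these criteria.

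**What to change.** In Interim analyses {21b}:

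- keep the counts of 46 and 24, and the green rate of 0.28, as they are;
- change the amber rate from 0.12 to 0.15;
- write the amber band as 24 to 45, so that green (46 or more), amber and red (fewer than 24) are mutually exclusive.

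If the pilot decision has already been taken, report the number randomised and the rate per centre-month to which the criteria were applied, so that a reader can check the decision.

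The cost is a correction to one sentence and, where relevant, one line of reporting. There is no operational cost.
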